Few studies have investigated whether baseline characteristics moderate the effect of different coaching levels. Of the 20 baseline moderators tested in the OurRelationship program, only 2 significant interactions with coaching level emerged. First, those with higher baseline levels of depressive symptoms were actually less likely to complete the program when receiving 4 coach calls compared with the stand-alone version of the program [32]. Second, those who identified as Hispanic were more likely to complete the program with 4 coach calls than in the stand-alone version. However, race, ethnicity, and household income did not moderate differences in program or treatment gains between one and 4 coach calls [37]. A similar pattern of findings emerged when investigating web-based interventions for individuals with stress and anxiety symptoms [39]. A host of candidate variables (eg, age, gender, level of education, occupation, computer expertise, time perspective, perceived treatment credibility, levels of internal or external motivation, and therapist bond) were examined to determine whether background variables moderated the effect of a coach in adherence to the intervention or treatment benefits; however, none of these baseline characteristics acted as between-group moderators [39].

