### Measures: Predictor Variables

#### Demographic Variables

Although support for demographic variables and their relationship to treatment adherence varies, a host of demographic variables will be included as candidate predictor variables. Predictor variables include race, ethnicity, household income, age, gender, as well as identifying as a same-gender couple.

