#### Baseline Measures of Relationship and Individual Symptomology

In line with the consistencies in previous research and in addition to relationship satisfaction, several measures of relationship symptomology will be used as possible candidates to predict program completion and gains in relationship satisfaction.

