#### Data Analysis Plan for Aim 2: What Are the Most Important Within-Group Predictors?

The second research question is: what are the most powerful predictors of treatment adherence and gains in relationship satisfaction within (1) the full-coach condition, (2) the automated coach condition, and (3) the contingent coach condition? If, in aim 1, the interaction terms result in a lower RMSE, better sensitivity, or better specificity, models will be constructed based on treatment assignment (ie, OurRelationship or ePREP) and coach assignment (ie, full, contingent, or automated). One statistically powerful way to test the most potent predictors of treatment adherence and gains is through the use of variable importance (VIMP). VIMP is a nonparametric approach within the random forest algorithm, which can help investigators identify which variables play a key role in predicting a binary (eg, program completion) or continuous (eg, improvements in relationship satisfaction) variable [53]. VIMP has been calculated in many ways in the past; however, one way that has shown promise has been through permutation (ie, Briemen–Cutler) importance [53]. This method randomly changes a given variable’s out-of-bag data and compares and averages the permuted prediction error with the original error resulting in VIMP [53]. This process not only helps identify which variables play a key role in prediction but also overcomes issues of overtesting using bootstrapping. Recent studies have used these out-of-bag estimates to generate CIs to test whether a variable has a meaningful effect in predicting an outcome with great success [53]. Indeed, these studies have suggested that 95% CIs that do not include zero will be assumed to have reliable predictors [53]. After identifying the most powerful predictors using VIMP, a multiple regression model will be estimated using the reduced set of variables to aid in the interpretation of the main effects, helping clinicians identify predictors of treatment adherence and gains.

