#### Data Analysis Plan for Aim 3: Predicting Between-Group Treatment Outcomes

Assuming that the models from the previous aim have levels of prediction accuracy, each of the within-group models will be used to generate predicted outcomes for each couple’s likelihood of adhering to the program as well as their treatment gains, creating counterfactual estimates of program completion and treatment gains as if each couple in the data set completed each intensity and method of coach contact [14].

To do this, the within-group models built in aim 1 will be used to generate potential outcomes for each couple’s likelihood of adhering as well as their gains in a (1) full coaching, (2) automated coaching, and (3) contingent coach conditions. If, in aim 1, the interaction terms result in a better RMSE, models will be constructed based on treatment assignment (ie, OurRelationship or ePREP) and coach assignment (ie, full, contingent, or automated). The estimates between the conditions for each couple’s between-group treatment differences between the full and automated coaching conditions can be understood as:

where 
[figure not shown]
 is the between-group likelihood of treatment adherence or gains for couple x, *Ŷ*(*x, Full Coach*) is the within-group likelihood of treatment adherence or gains for couple x in the full-coach condition, and *Ŷ*(*x, Contingent Coach*) is the within-group likelihood of treatment adherence or gains for couple x in the contingent coach condition [14]. These hypothetical between-group outcomes will then serve as dependent variables in a second random forest to calculate VIMP, which will identify the most powerful predictors of between-group differences. After identifying the most powerful predictors using VIMP, a multiple regression model will be estimated using the reduced set of variables to aid in the interpretation of the main effects. This process will thereby help clinicians determine which couples should be assigned to which level of coach contact.

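### Aim 3 analyses differences between two fitted forests as if they were observed outcomes, so first-stage estimation error is reported as moderation of the coaching effect

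*Protocol article*

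**What the plan says.** The protocol article's data analysis plan for Aim 3 fixes four steps.

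- Prediction: "the within-group models built in aim 1 will be used to generate potential outcomes for each couple’s likelihood of adhering", and likewise for gains in satisfaction, under full, automated and contingent coaching.
- Differencing: for each couple, one condition's prediction is subtracted from another's.
- Second stage: "These hypothetical between-group outcomes will then serve as dependent variables in a second random forest to calculate VIMP".
- Interpretation: "After identifying the most powerful predictors using VIMP, a multiple regression model will be estimated using the reduced set of variables". The output is meant to help clinicians decide which couples get which level of coach contact.

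Aim 3 has one entry condition, with no threshold: "Assuming that the models from the previous aim have levels of prediction accuracy". It gives no declaration rule of its own. The only rule is in the Aim 2 plan: "95% CIs that do not include zero will be assumed to have reliable predictors". That section also says that bootstrapping within the VIMP method deals with overtesting.

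**The concern.** The second-stage dependent variable is not data on couples. It is the output of two models that have already been fitted to the candidate predictors, with most couple-level outcome noise averaged away. Explaining it with those predictors shows how well one model reproduces two others. It does not show whether a predictor changes the effect of coaching. Resampling the second stage does not help, because the first-stage error is common to all scored couples and is held fixed.

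Aim 3 is the step intended to guide coaching assignment, so a long list of false moderators would have practical consequences. The no-moderator case is realistic on the article's own review (The Effect of Having a Coach on Program Outcomes). Of 20 moderators tested in OurRelationship, 2 interacted with coaching level. In a stress and anxiety study, "none of these baseline characteristics acted as between-group moderators".

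**Working it through.** **Mechanism.** Write the constructed outcome for a couple with predictors x as D(x) = Ŷ(x, full) − Ŷ(x, other) = τ(x) + [e_full(x) − e_other(x)]. Here τ(x) is the true coaching effect and each e is the estimation error of one fitted forest. With no moderation τ(x) is constant, so all variation in D comes from e_full(x) − e_other(x), which is a function of x. Scoring more couples shrinks the second-stage standard errors but leaves that error unchanged.

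**Inputs from the article.**
- Participants: 226 + 145 + 145 + 222 + 143 + 143 + 224 = 1248 couples, which reproduces the stated total.
- Pooled over programs: full coach 226 + 222 = 448; automated 145 + 143 = 288; contingent 145 + 143 = 288. Full versus automated and full versus contingent therefore have the same sizes.
- Predictors: 6 demographic ("Predictor variables include race, ethnicity, household income, age, gender, as well as identifying as a same-gender couple"), 7 relationship measures including baseline satisfaction, 4 external stress and 2 motivation: 6 + 7 + 4 + 2 = 19, each counted once.
- Chance expectation at the 5% level: 19 × 0.05 = 0.95.

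**Assumptions not in the article.** Predictor correlation 0 or 0.2; prognostic R² 0 or 0.15 with identical effects in both conditions; 300 trees per forest; continuous gain, or completion at about 65%; own-condition predictions either in-bag or out-of-bag.

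**Simulation with no true moderator.** Forests were fitted in 448 and 288 couples and all 1248 couples were scored. The difference was then analysed by a second forest with permutation VIMP, and by regression. There were 15 settings with 12 replicates each. Entries are the range over settings of the mean number flagged out of 19.

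| Rule | All settings | Prognostic R² 0.15 only |
|---|---|---|
| 95% VIMP interval excludes zero (delete-d jackknife) | 10.3 to 14.8 (overall 12.5) | 10.7 to 13.8 |
| Same, subsampling standard error | 10.8 to 14.9 | 10.9 to 14.1 |
| Regression on all 19, p<0.05, in-bag own-condition scores | 8.6 to 10.6 | 8.7 to 10.4 |
| Same, out-of-bag own-condition scores | 10.9 to 13.3 | 10.9 to 12.6 |
| VIMP selection, then p<0.05 in the reduced regression | 6.8 to 11.0 | 7.3 to 10.0 |
| Direct predictor-by-condition interaction on observed outcomes | 0.4 to 0.8 | 0.6 to 0.8 |

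The second forest explained 19% to 56% of the variance of a difference that contained no moderation. With waitlist couples left out (40 runs per outcome), regression on all predictors flagged 11.2 and the direct test 0.9.

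**Is the interval method to blame?** A pure-noise outcome in the same second forest gave 0.6 to 0.8 of 19 by the VIMP interval. The excess therefore comes from the constructed outcome.

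**Per-program sizes.** If Aim 1 leads to separate models by program, the sizes are 226 versus 145. Regression on all 19 then flagged about 10, against about 12 at 448 versus 288 in the same simulation and about 1 from direct interaction tests, with or without prognostic effects.

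**The case against.** The strongest objection is the accuracy condition. With no predictor effects at all, the within-condition forests have nothing to predict and Aim 3 should not be run. Simulations of that case (12.8 of 19 for a continuous and 13.1 for a binary outcome by VIMP interval, in separately coded runs) should not carry the argument. This stands, but it does not remove the problem. The condition has no threshold, and prognostic factors shared by all conditions can satisfy it. The R² 0.15 column is that case.

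Second, Aim 3 does not state the interval rule and mentions no p values. VIMP may only be ranked, and the regression is described as an aid to interpretation. This also stands: counts of declared predictors depend on carrying the Aim 2 rule over. But a bare ranking would, under no moderation, still be a ranking of noise.

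Third, Aim 3 has no stated hypothesis, the article condenses a fuller plan, and the method is attributed to a cited source not available here. The use of predicted differences as the dependent variable is nevertheless stated outright, and so is the clinical use of the result.

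A reader might infer that the plan will falsely declare some particular number, such as 13 of 19, or that it commits to significance testing of predicted differences. The documents support neither. Correlations, tuning, scoring method and the coding of race and ethnicity are not given, and Aim 3 names no test. Nor does the point show that real moderators are absent, only that this procedure cannot tell them from estimation error.

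**Conclusion.** The concern holds. As described, Aim 3 would present first-stage estimation error as moderation. With no true moderator, roughly 9 to 15 of 19 predictors would be flagged, or about 7 to 11 if both VIMP and the follow-up regression must be passed, against about 1 expected. The conclusion is the same for in-bag and out-of-bag scoring, for continuous and binary outcomes, and with or without shared prognostic effects.

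The size rests on the assumptions listed in the working and on the Aim 2 interval rule applying to Aim 3. The forests were not run in the R package named under Missing Data, and 12 replicates per setting leave some Monte Carlo error, far smaller than the gap from nominal. It should be corrected before Aim 3 is analysed. The Results section says that only completion rates have been examined, and the Procedure section says that preregistration is still to come, so there is time.

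**What to change.** Base Aim 3 conclusions on predictor-by-coaching interactions tested on the observed completion and satisfaction outcomes, in one model across the conditions compared. The model must respect the two-stage route described under Procedure: contingent and continued automated coaching are separated by a second randomisation of nonadherent no-coach couples, so full versus contingent is not a simple one-stage contrast. The article gives achieved counts but no allocation probabilities. Any method that needs them must state them first. Direct tests still yield about 0.95 false positives per pair of conditions and outcome, so the plan should say how that is handled.

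If the two-forest difference is kept, use it descriptively. Compare its VIMP with a reference distribution from re-running the whole procedure (both condition forests, the difference and the second forest) with coaching labels permuted after condition means are removed. Attach no second-stage intervals or p values that treat predicted differences as observed data. State whether the Aim 2 interval rule applies to Aim 3.

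The cost is plan wording and more computing, with no new data. The downside is that fewer predictors will be declared.

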### Missing Data

Finally, because missing data are anticipated, all missing data will be imputed using the miss-forest algorithm of Ishwaran and Kogalur randomForestSRC package in R (R Foundation for Statistical Computing) [54]. Miss-forest has been shown to robustly impute missing data without overfitting even if the types of data are mixed, there are interactions, or the data are high dimensional [55].

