These models will be built using the random forest algorithm [52]. The random forest algorithm reduces overfitting by bootstrapping or fitting several different trees to subsets of the sample to inform the predictions (ie, bagging) [52]. Once the ensemble of trees is generated, the outputs from all the trees are aggregated, and the prediction is generated. Its ability to predict treatment outcomes for individuals and couples has been proven in several precision medicine studies [13,14]. Thus, in the first aim of this study, the random forest algorithm will be used to accurately predict the within-group likelihood that a couple completes the OurRelationship and ePREP programs in (1) the full-coach condition, (2) the automated coaching condition, and (3) the contingent coach condition as well as the magnitude of their gains in relationship satisfaction. The model characteristics address the model performance on the test data set*.* For binary outcomes (program completion), the model characteristics used to evaluate the validity of the model include sensitivity, specificity, positive predictive value, and negative predictive value of the model built on the test data set (Figure 1). Model sensitivity is measured by the percentage of true positives (ie, a/a+c). Model specificity is the percentage of true negatives (ie, d/d+b). A model’s positive predictive value yields a positive test result and the probability that the participant will complete the program (ie, a/a+b). Finally, a model’s negative predictive value yields negative test results and the probability that the participant will not complete the program (ie, d/d+c). Good models for binary outcomes include models whose sensitivity, specificity, positive predictive value, and negative predictive value are closest to 1. For continuous outcomes (ie, improvements in relationship satisfaction), model accuracy will be evaluated using the RMSE. The RMSE is a measure of absolute fit and is the square root of the variance of the residuals; smaller values indicate better fit.

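### Imputing follow-up satisfaction with a forest and then scoring forests on the imputed values makes the reported RMSE too small

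*Protocol article*

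**What the plan says.** The Missing Data section states that "because missing data are anticipated, all missing data will be imputed using the miss-forest algorithm". No variable is excepted, so the rule covers the continuous outcome, gain in relationship satisfaction, as well as the predictors. The section's only defence of the method is that "Miss-forest has been shown to robustly impute missing data without overfitting even if the types of data are mixed".

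The analysis model belongs to the same class as the imputer. The Aim 1 plan says "These models will be built using the random forest algorithm" and, on evaluation, "The model characteristics address the model performance on the test data set". For satisfaction, "model accuracy will be evaluated using the RMSE", with smaller values read as better fit. For program completion the measures are "sensitivity, specificity, positive predictive value, and negative predictive value of the model built on the test data set". Nothing restricts the test data to couples whose follow-up satisfaction was observed.

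Aim 2 ranks predictors by permutation importance (VIMP): "This method randomly changes a given variable’s out-of-bag data and compares and averages the permuted prediction error with the original error resulting in VIMP". Its decision rule is that "95% CIs that do not include zero will be assumed to have reliable predictors".

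**The concern.** When a forest fills in a missing outcome, the value is close to a conditional mean given the other variables. It lacks the scatter that a real couple's score would have. A second forest tested against it is largely graded on agreement with a similar model. That agreement is good whether or not either model predicts real couples well, so RMSE improves as more outcomes go missing.

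The aim of Aim 1 is to report how well outcomes can be predicted, and RMSE is the only accuracy measure named for satisfaction gains. The error is in the favourable direction. Aim 3 takes the accuracy of these models as its starting point, and its results are meant to guide which couples receive which level of coach contact.

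**Working it through.** **Inputs.** The article states no missing-data rate and no RMSE, so there is no published figure to reproduce. The missing share m is assumed at 10% to 40%. Pooled over programs, the Participants section gives 226 + 222 = 448 full-coach couples, and 145 + 143 = 288 couples in each of the contingent and automated groups.

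**Approximation.** For one fitted forest,

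MSE_apparent = (1 − m) × MSE_observed + m × D,

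where D is the mean squared distance between that forest's predictions and the imputed outcomes. If imputed outcomes carry no residual, D is near zero and RMSE_apparent / RMSE_true tends to √(1 − m):

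| m (assumed) | √(1 − m) | RMSE too small by |
|---|---|---|
| 10% | 0.949 | about 5% |
| 20% | 0.894 | about 11% |
| 30% | 0.837 | about 16% |
| 40% | 0.775 | about 23% |

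This needs only that imputed outcomes sit in the test set. It does not depend on whether imputation comes before the split.

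**Simulation.** Outcomes were missing completely at random, imputed by a generic forest, then split 70/30. The package named in the article was not used. In one set (288 couples, 19 predictors, 20 replicates per cell) the ratio of apparent to true RMSE was 0.95 to 0.96 at 10% missing, 0.87 to 0.89 at 20%, and 0.84 at 30%. A second set used 18 predictors, three of them real when R² = 0.2, with 100 replicates at R² = 0 and 25 at R² = 0.2:

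| R² | Couples | m | Apparent RMSE | RMSE on new data | Ratio |
|---|---|---|---|---|---|
| 0 | 448 | 10% | 0.954 | 1.022 | 0.934 |
| 0 | 448 | 20% | 0.905 | 1.019 | 0.888 |
| 0 | 448 | 30% | 0.849 | 1.019 | 0.834 |
| 0.2 | 448 | 10% | 0.875 | 0.940 | 0.931 |
| 0.2 | 448 | 30% | 0.776 | 0.945 | 0.822 |
| 0.2 | 288 | 30% | 0.762 | 0.948 | 0.803 |

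Some ratios fall slightly below √(1 − m). Replicates are few, and imputing before the split may add some leakage, so the formula is a guide rather than a strict limit. With R² = 0.2, 448 couples and 30% missing, fitting and scoring on observed outcomes only gave 0.937 against 0.945 on new data, which is essentially unbiased.

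**VIMP at 30% missing, 448 couples.** Mean VIMP of null predictors was 0.00248 with imputed outcomes against 0.00008 with observed outcomes only (R² = 0), and 0.00158 against 0.00026 (R² = 0.2). For true predictors, raw VIMP was not inflated (0.0735 against 0.0774). It rose only relative to outcome variance (0.0990 against 0.0758). The confidence-interval rule itself was not simulated.

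**Completion.** The Results denominators equal twice the couples minus withdrawals: 2 × 226 − 4 = 448, 2 × 145 − 2 = 288 (twice) and 2 × 222 − 3 = 441. The two smaller ePREP groups give 284 (contingent) and 283 (automated), where the Results show 283 and 284. These look swapped, but the total is the same. Completion thus appears fully observed among retained participants.

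A separate route would exist if the imputer used completion to fill in predictors. With 288 couples and six null predictors, each 20% missing, the out-of-bag area under the ROC curve was 0.554, against 0.493 with complete predictors (25 replicates). The article does not say which variables enter the imputer.

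**The case against.** The strongest reply is that this is a condensed article. It does not state that imputation is single, that it precedes the train/test split, or exactly how the named package fills a value, and a preregistration is announced. That stands for those details: a reader might infer leakage from test to training data, or VIMP intervals that ignore imputation uncertainty, but the text fixes neither. It does not remove the core point. The instruction to impute everything, outcomes included, is stated, as is RMSE on an unrestricted test set.

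The size is also open to challenge. Scores are averaged over two partners, so a couple with one responder may keep much of its residual. For illustration, assume that 20% of couples are affected, half of them with one responder, and that partner residuals correlate 0.6. The couple-average residual variance is (1 + 1 + 2 × 0.6)/4 = 0.80 when both respond. It is ((1 + 0.6)/2)² = 0.64 when one is imputed from the other, a ratio of 0.8. Overall, 0.8 + 0.1 × 0.8 = 0.88 and √0.88 = 0.938, so RMSE is about 6% too small rather than 11%. This objection stands and makes the tabulated figures upper values.

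Finally, no stated decision is shown to flip. Aim 3 presumes adequate accuracy but sets no threshold. The choice between three and six models compares two RMSEs on the same data, where a shared understatement need not alter the result. Both observations are fair. What is wrong is the reported accuracy itself.

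**Conclusion.** The plan is wrong as written for the RMSE of relationship-satisfaction gains. Followed literally, it understates RMSE by up to about 5%, 11%, 16% and 23% at 10%, 20%, 30% and 40% of couple outcomes imputed, and by less where one partner responded. These sizes rest on an assumed missing rate, on imputed values with little residual and, for the simulations, on data missing completely at random and a generic imputer. The claim that the imputer does not overfit is no answer, because it concerns the quality of imputation and not the scoring of a model against values that a similar model produced.

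Three stronger readings are not supported:

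- **Completion accuracy.** A reader might infer that sensitivity, specificity and the predictive values are inflated too. Completion appears fully observed, so outcome imputation does not affect them.
- **All importance scores.** VIMP of null predictors can rise, but raw VIMP of true predictors did not.
- **Different bias by coaching level.** This would need follow-up loss to differ between conditions. The article gives no follow-up rates, so it remains a possibility.

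**What to change.** Amend the Missing Data section, and carry the wording into the preregistration, so that:

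- outcomes are not imputed when model performance and VIMP are computed;
- RMSE is scored only on couples with observed follow-up satisfaction, with a stated rule for couples with one responding partner;
- predictors are imputed without the outcome and without test-set data;
- the order of imputation and splitting, and the number of imputations, are stated.

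Missing satisfaction can be addressed in a sensitivity analysis, either by weighting for response or by multiple imputation with residual draws. Which of the two is a matter of preference.

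The cost is a change of wording and analysis code. The reported RMSE will be larger and the scored sample smaller. According to the Results section only completion rates had been analysed at the time of writing, so the change could be made before satisfaction was examined.

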### Participants

A total of 226 couples were randomly assigned to the OurRelationship coach condition, 145 couples were assigned to the OurRelationship contingent coach condition, and 145 couples were assigned to the OurRelationship automated (ie, email only) condition. Similarly, 222 couples were assigned to the ePREP coach condition, 143 couples were assigned to the ePREP contingent coach condition, and 143 couples were assigned to the ePREP automated (ie, email only) condition. A total of 224 couples were assigned to the waitlist control condition. In total, 4 individuals from the OurRelationship coach condition, 2 from the OurRelationship contingent coach condition, and 2 from the OurRelationship automated condition asked to discontinue and have their data removed from the study. Furthermore, 3 individuals from the ePREP coach condition, 2 from the ePREP contingent coach condition, and 3 from the ePREP automated condition asked to discontinue and have their data removed from the study.

In total, 47.5% (1178/2480) of the sample identified as male, and 52.5% (1302/2480) of the sample identified as female. The average length of the relationship was 5.74 years (SD 5.18). Most of the participants reported belonging to an opposite-gender relationship (2318/2480, 93.47%), and a smaller percentage were in same-gender relationships (162/2480, 6.53%). Most participants identified as White non-Hispanic (1520/2480, 61.29%), fewer identified as Black (434/2480, 17.5%), White Hispanic (279/2480, 11.25%), Black Hispanic (28/2480, 1.13%), American Indian or Alaskan Native (23/2480, 0.93%), Asian (17/2480, 0.69%), Hawaiian or Pacific Islander (4/2480, 0.16%), and Biracial (86/2480; 3.47%); and 3.59% (89/2480) of participants belonged to a race that was not listed. Furthermore, 6.81% (169/2480) of participants did not have a degree or diploma, 12.3% (305/2480) had earned a general education diploma, 14.23% (353/2480) had completed high school, 8.23% (204/2480) had a technical or vocational certification, 22.54% (559/2480) had some college degree, 8.83% (219/2480) had graduated with an associate’s degree, 10.69% (265/2480) had a bachelor’s degree, and 2.38% (59/2480) had a master’s or advanced degree.

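### Read plainly, the missing-data section pools all conditions in one miss-forest imputation, which would shrink Aim 3's coaching contrasts for relationship satisfaction

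*Protocol article*

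**What the plan says.** The Missing Data section is two sentences long. Values are to be filled "because missing data are anticipated", and "all missing data will be imputed using the miss-forest algorithm", with an R package named. The second sentence supports the choice by saying that the method works "without overfitting even if the types of data are mixed, there are interactions". The section does not say whether the imputation is pooled or done by condition, whether condition is an imputation variable, whether waitlist couples are included, or how much is missing.

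The analyses that use the completed data are condition-specific. Aim 1 builds models within each coaching level, or within program by coaching level. Aim 3 applies these models to every couple, "creating counterfactual estimates of program completion and treatment gains". It takes the difference between two conditions' predictions and makes that difference the outcome of a second forest.

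**The concern.** In a pooled forest, condition is one or a few columns among about 20 predictors, and its effect on satisfaction is probably small. Many trees never split on it, or split on it only high up. A missing follow-up score in one condition is then filled largely with the value typical of similar couples in all conditions. The imputed part of the data carries a weakened coaching effect and a weakened predictor-by-coaching effect, and these are the two quantities that Aim 3 is meant to find. Naming interactions as a strength of the method reassures on exactly the property that is at risk.

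The bias is toward zero, so coaching levels would look more interchangeable for satisfaction gain than they are. Other conditions' relations would also leak into the within-group satisfaction models of Aims 1 and 2.

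**Working it through.** **Inputs from the article (Participants section).** "A total of 226 couples were randomly assigned to the OurRelationship coach condition, 145 couples were assigned to the OurRelationship contingent coach condition", with 145 automated; "222 couples were assigned to the ePREP coach condition, 143 couples were assigned to the ePREP contingent coach condition", with 143 automated; "A total of 224 couples were assigned to the waitlist control condition".
- Total: 226 + 145 + 145 + 222 + 143 + 143 + 224 = 1248 couples, which reproduces the stated total.
- Over programs: full 226 + 222 = 448, contingent 145 + 143 = 288, automated 145 + 143 = 288.

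**Assumed, because the article gives no figure:** the missing share of follow-up satisfaction (m) and the sizes of the coaching effect and the predictor-by-coaching slope.

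**Expected direction.** Let D be the true full-minus-automated difference and k the fraction of it that the forest keeps in its imputed values. With the same m in both conditions:

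D(imputed) ≈ (1 − m)D + m·k·D, so the relative loss ≈ m(1 − k).

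If condition is left out, k = 0 and the loss is about m. If it is included, k is unknown and has to be simulated.

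**Simulation A.** 448/288/288/224 couples; 20 correlated predictors; true difference 0.3 and true slope 0.3 (outcome SD about 1). The outcome was missing at random given one baseline predictor. Imputation was by a single random forest (100 trees, one third of the columns per split), with 30 replicates. Effects were estimated by ANCOVA with an interaction; Monte Carlo SE 0.007 to 0.018. The two pooled figures for the difference are for condition entered as dummies and as one column.

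| m | Quantity | Full data | Pooled, condition in | Loss | Within condition | Loss |
|---|---|---|---|---|---|---|
| 20% | difference | 0.315 | 0.278 / 0.286 | 12% / 9% | 0.315 | 0% |
| 20% | slope | 0.307 | 0.248 | 19% | 0.269 | 12% |
| 35% | difference | 0.285 | 0.227 / 0.238 | 20% / 16% | 0.286 | 0% |
| 35% | slope | 0.286 | 0.206 | 28% | 0.244 | 15% |
| 50% | difference | 0.275 | 0.185 / 0.202 | 33% / 27% | 0.273 | 1% |
| 50% | slope | 0.304 | 0.176 | 42% | 0.238 | 22% |

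- Condition left out, m = 35%: difference 0.187, a 34% loss, as the formula predicts for k = 0.
- Condition in, m = 35%: k = 1 − 0.204/0.35 = 0.42 to 1 − 0.165/0.35 = 0.53. The pooled forest keeps about half of the contrast.
- Using 22% or all of the columns per split at m = 35%, the difference still fell 17-23% and the slope 27-33%.

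**The Aim 3 procedure itself** (condition-specific forests, then the difference of predictions; setting A, m = 35%):

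| Data used | Mean difference | Slope |
|---|---|---|
| Full data | 0.286 | 0.172 |
| Pooled, condition in | 0.233 to 0.242 | 0.121 to 0.122 |
| Within condition | 0.288 | 0.149 |
| Observed scores only | 0.289 | 0.152 |

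Pooling costs 15-19% of the difference and about 29% of the slope.

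**Other assumptions, waitlist not in the forest, condition in:**
- B: true effects 0.20, missing completely at random. The difference and slope fell 16% and 18% at m = 20%, and 32% and 28% at m = 35%. Within program-by-coaching groups the difference was 0.199-0.201 against 0.209 (4-5% lower).
- C: the six program groups at their actual sizes, true effects 0.25, missing at random. The falls were 11% and 15% at m = 20%, and 25% and 36% at m = 40%. Within groups the difference was intact and the slope lost 9% and 21%.
- D: true effects 0.20, missing completely at random, 20 runs. At m = 30% the difference went from 0.199 to 0.138 (31%) and the slope from 0.201 to 0.146 (27%). Within condition they were 0.180 and 0.178 (10% and 11% lower).

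**Completion.** 2 × (1248 − 224) = 2048 program participants, less 16 who had their data removed, is 2032. The completion denominators in the Results section sum to 448 + 288 + 288 + 441 + 283 + 284 = 2032. Completion is therefore reported for every retained participant and leaves almost nothing to impute.

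**Limits.** The simulations used a general-purpose random-forest regressor, not the R package that the article names, and only the outcome was missing.

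**The case against.** The strongest reply is that the criticised procedure is not written down. The word 'all' says which values are filled, not that every couple enters one forest. The models are condition-specific, so imputing by condition would also fit the text. The article says that its analyses will be preregistered, and run structure could be settled there. This stands in part: a reader might infer that the article commits to a pooled run, and it does not. But it gives one undivided step, and its only supporting argument, robustness to interactions, does not hold for the plain reading.

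A second reply is that the analysts would include condition as an imputation variable. That reduces the loss but does not remove it.

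A third is that forest shrinkage matters more than pooling. In simulation A a true slope of 0.30 is estimated as 0.172 by the Aim 3 procedure with nothing missing, a loss of 0.128. Pooling rather than imputing within condition costs a further 0.149 − 0.121 = 0.028. This is correct, and it means that not all of the slope loss comes from borrowing across conditions. The pooling part is still avoidable at little cost.

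**Conclusion.** The point holds in a limited form. If the missing-data section is followed as it plainly reads, Aim 3's satisfaction contrasts are biased toward zero. With assumed effects of 0.2 to 0.3 SD and condition in the forest, the mean difference falls by about 10-15% at 20% missing (simulated 9-16%) and about 15-30% at 35-40% missing (simulated 16-32%). The slope falls by about 15-20% and 28-36%. These sizes are illustrative, since the article gives neither the missing rate nor an effect size.

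Stronger readings are not supported:
- **That the loss generally equals the missing share.** This is about right when condition is left out or the effect is near 0.2 SD, but with effects of 0.3 the loss in the mean difference is nearer half of that share.
- **That couples would be assigned to the wrong coaching level.** No simulation examined assignment or the variable-importance ranking.
- **That waitlist couples contaminate the program arms.** The article does not say that they enter the same imputation; the risk is conditional. They are 224/1248 = 18% of couples.
- **That all of Aim 3 is affected.** Only relationship satisfaction is exposed.
- **That imputing within condition is a full cure.** It restores the mean difference fully or nearly so, but about 10-20% of the slope is still lost to smoothing (22% at 50% missing in simulation A).

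**What to change.** State in the Missing Data section, and in the preregistration, that relationship satisfaction is imputed separately within each coaching level, or within each program-by-coaching group if Aim 1 leads to six models. Waitlist couples should be kept out of the program-arm imputation. Drop or qualify the claim about interactions. Report the share of missing follow-up satisfaction by condition.

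Repeat the Aim 3 satisfaction contrasts in couples with observed follow-up scores and report both sets of results. This check is needed because within-condition imputation does not fully protect the predictor-by-coaching effects. In simulation A at 35% missing, the observed-score slope from the Aim 3 procedure (0.152) was about the same as after within-condition imputation (0.149).

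The cost is a sentence or two of text and a loop in the code. The downside is that each imputation forest has fewer couples (143 to 226 if split by program and coaching), so imputed values are somewhat noisier. The article reports that only completion rates had been analyzed, so at that stage the change could be made before any satisfaction result was known.
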